## 3. Materials and Methods

### 3.1. Setting

The primary investigator leading this study is an experienced and dedicated midwife who actively practices in a private hospital, along with regular rotations through multiple public hospitals. This diverse practice setting offers a valuable opportunity to include pregnant women from at least three distinct health centers, encompassing a wide range of profiles and characteristics among the participants.

### 3.2. Design

This study employs a robust multicenter randomized controlled single-blind experimental design. The intervention group will receive acupressure applied to specific points that will be thoroughly explained later in the study. As for the control group, acupressure will be administered to points that, according to traditional Chinese medicine’s energy meridians, are deemed to lack the desired therapeutic effect. Due to the fact that the principal investigator is directly responsible for both administering the intervention and the placebo, the study cannot be designed as a double-blind trial. To ensure transparency and impartiality, the collected data will be provided anonymously to a secondary investigator who will conduct the statistical analysis without any indication of which group represents the control or intervention.

### 3.3. Sampling and Sample Size

The sampling process will be conducted using an intentional or convenience sampling approach, wherein all pregnant women who meet the inclusion criteria and are under the care of the project’s principal investigator will be included until the predetermined sample size is reached. This meticulous approach aims to encompass a diverse range of participants, thereby enhancing the generalizability of the study findings.

The calculation was based on the results obtained in a pilot study (unpublished data) with 17 and 23 women in the intervention and control groups, respectively, using the Gpower 3.1.9.4 software. Different calculations were carried out based on the means and standard deviations obtained in the times of the active, passive, and expulsive phases, as well as on the VAS scale (Likert 1–10 points) used to measure pain. From the different calculations carried out, the one that determined the largest sample size (difference of means in time of expulsive phase) was selected with the intention of having sufficient statistical power for all the analyses proposed.

The means and standard deviation obtained for the expulsive phase time (second stage of parturition, which starts at full dilation and continues until birth) in a pilot study were 46 ± 39 min for the intervention group and 65 ± 47 min for the control group. The number of women per group was calculated to determine a difference in the means of independent groups with alpha = 0.05 (type I error), power (1-beta) = 0.8, and allocation n1/n2 ratio = 1, obtaining a total of 166 women (83 in each group) [23].

Recruitment. The selection of participants for this study will adhere to specific criteria outlined as follows:

Inclusion criteria: The study will include pregnant women who meet the following requirements: Women with induced, accelerated, or spontaneous labor, both primiparous and multiparous, are included.Women who are 18 years of age or older and in the term of their pregnancy (37–42 weeks).Single gestation (not multiple pregnancies).Absence of associated pathologies or medical conditions.Proficient communication skills in the Spanish language.

Exclusion criteria: The study will exclude pregnant women who meet any of the following criteria: Women with a fetus in a breech or transverse presentation.Women who have previously undergone caesarean sections.Women with existing skin lesions or wounds.Women with cognitive deficits or impairments.Women who have consumed toxic substances or medications during their pregnancy.Women with diagnoses of placenta previa (previous insertion placenta), fetal pathologies such as Delayed Intrauterine Growth (DIC) or Small for Gestational Age (SGA), or instances of oligo- or polyhydramnios.

These well-defined criteria will ensure that the study focuses on a specific group of pregnant women, enabling researchers to examine the intended effects of the intervention more accurately. 

Allocation. Assignment to the intervention group will be made by simple randomization of the sample. To do this, a random sequence of numbers will be generated using R software (R 4.1.3, March 2022), which is open source and specifically designed for statistical analysis, to assign women to intervention/control groups. For this purpose, the function will be used: sample (1:166, 83, replace = FALSE). The women who are attended in the order of arrival will be included in the intervention group if their order coincides with any of the random numbers generated.

Intervention. Intervention will be implemented by a single researcher and it will be based on pressure on the points detailed below:

It will start by exerting pressure on:-LI4 of the left hand, SP6 of the left leg, GB21 of the left shoulder, and then the same sequence on the right side. This is intended to generate regular and effective contractions and promote the descent of the fetal head.-Yongquan (R1): For pain relief and relaxation of women, exerting constant pressure for 1 min, as many times as necessary to promote pain control.-Hand points: Also for pain relief, autonomously by the woman, whenever she needs it.

The location of the trigger points can be visualized in Appendix A.

Constant pressure will be generated for 3 min, alternating points, and repeating the technique every 4 h, after the scans. Digital pressure will be applied until half of the nail turns white (equivalent to 3 to 5 kg of pressure) [23]. The Hegu point (LI4) will also serve as an analgesic point.

Based on the research carried out by Dávila Payano and Lazo del Carpio (2016), as for the main researcher, it is essential to maintain a deep and relaxed breath, and to apply deep and lasting pressure, bearing all the weight on the pressure point during the exhalation. Your position will be static, standing, with legs slightly apart, exerting force with your body weight. The manipulation must be constant, energetic, uniform, and delicate, using fingers or knuckles [21].

Control. The control group will receive the application of the technique on points not identified by acupuncture as key points (placebo), but with the same characteristics described above (time, frequency, pressure). Different points will be used as placebo points and will be determined using some of the potentially therapeutic points as references; some of these points will be one F-Cun away from the original points with therapeutic effect. The Cun measurement, derived from acupuncture anatomy, represents the width of the thumb at the joint level and serves as an important anatomical unit in traditional acupuncture practices. In traditional Chinese medicine and acupuncture, the concept of Cun plays a vital role in determining precise anatomical locations for treatment. It is a unit of measurement utilized to establish the distances between acupuncture points on the human body. The Cun measurement is unique to each individual and is derived from the width of the thumb at the joint level. By using the Cun measurement as a standardized reference, acupuncturists can accurately locate specific points for therapeutic intervention. In this study, the F-Cun distance will be employed as a reference point for the placement of placebo points, ensuring consistency and precision in the experimental design [23]. The control points placed an F-Cun away from real acupoints will be GB21 (on the shoulder) and another one will be placed between the knuckles of the index and middle fingers. Additionally, the last one will be 2 F-Cun higher than the SP6 placement (see exact placement in pictures at the end of this paper).

The purpose behind administering pressure to different points using fingers in the control group is to eliminate any potential placebo effect associated with “manipulation using a therapeutic instrument”. It is important to note that none of the points pressed in either the intervention group or the control group possess an anatomical location that can induce significant physiological changes when pressure is applied, such as pressing the carotid artery. This precautionary measure ensures the safety of the study participants, minimizing any adverse effects resulting from the applied pressure on the women. Thus, the inclusion of these additional control points not only serves to rule out placebo effects, but also guarantees the well-being and welfare of the participants by preventing any unintended consequences arising from the pressure applied during the study.

Outcomes. Variables will be measured in order to assess the efficacy and safety of the intervention:-Effectiveness of the use of acupressure on labor times in minutes (time of cervical dilatation and time of fetal expulsion according to the recommendations of the World Health Organization).-Effectiveness of the use of acupressure on women’s perceived pain by recording values on the VAS scale and the need for pharmacological analgesic methods. A Visual Analogue Scale (VAS) is a pain rating scale that was first used in 1921 by Hayes and Patterson. The pain VAS is a one-dimensional measure of pain intensity that is used to record the progression of patients’ pain or to compare the severity of pain between patients with similar conditions. The patient must rate their perceived pain on a scale of 0 (no pain) to 10 (the most severe pain imaginable) [1,4,13,14,15,17,19,24,25,26].-Impact of the use of acupressure on maternal satisfaction expressed about the childbirth experience (using the validated satisfaction scale Mackey Satisfaction Childbirth Rating Scale—MSCRS) [8].-Impact of the use of acupressure on neonatal outcomes (Apgar test at 1/5/10 min and arterial blood gases at birth).

Independent variables.-Sociodemographic: Age (years), country of birth, weight (kg), height (cm), marital status (single, domestic partner, married, divorced, widowed), studies (primary, secondary, superior, postgraduate), employment (employed, unemployed), dysmenorrhea: yes/no (verbalization by the woman of having painful menstruations), fear of childbirth (yes/no), reasons for fear of childbirth (verbalization by the woman), hospital (public/private).-Clinics: date of last period (FUR) and probable date of delivery (FPP), gestational age (weeks of gestation), obstetric formula (pregnancies, abortions, childbirth), estimated fetal weight (kg), fetal weight at birth (kg), type of delivery termination (eutocic, instrumented, caesarean section), special circumstances associated with childbirth (maternal fever, meconium, cord prolapse, antepartum hemorrhage, and uterine rupture), factors associated with the newborn (abnormal registration and altered arterial pH, considering normal values—arterial pH at birth: 7.25–7.45, blood oxygen (PaO2): 60–80 mmHg, blood carbon dioxide (PaCO2): 35–45 mmHg, bicarbonate (HCO3-): 24–26 mEq/L, base excess: ±3.0).-Variables that can affect the effectiveness of the intervention: hospital shift the night before (yes/no), start time of application of the technique (0–24 h), level of saturation of the system (number of women in the service attended by the researcher).

Data analysis. The data obtained will be analyzed with IBM SPSS Statistics v23 software; this will allow for the descriptive analysis of qualitative variables through absolute frequencies and percentages, and of quantitative variables through measures of central tendency, dispersion, and position. On the other hand, a statistical inference analysis will be carried out to evaluate the possible differences between the groups; these will be treated as unpaired samples because there are different women who constituted each group.

The statistical association between qualitative variables will be analyzed using Pearson’s chi-square test or Fisher’s exact test (in 2 × 2 tables when in Pearson’s Chi square, the expected frequencies are less than 5 in more than 20% of the cells). Odd ratio will be calculated as size effect measure for this analysis.

For the comparison of means between dichotomous variables, the Student t-test and ANOVA test will be performed in the case of dichotomous or polytomous variables, respectively, as long as the parametric criteria are met (normality evaluated using the Kolmogorov–Smirnov test and homoscedasticity evaluated with the Levene test). If the parametric criteria are not met, non-parametric tests will be performed (Wilcoxon test and Kruskal–Wallis test, respectively). For the Student t-test analysis, Cohen’s d will be used as a measure of the effect size. 

For regression analysis, the Pearson correlation coefficient will be used. In the case of non-normal distributions, Spearman correlation test will be used. Statistical significance at 5% will be established for all tests.

Ethical aspects. The present study preserves the well-being of the subject above the interests of science or society and the ethical considerations that support it, as part of the compliance with current international and national regulations for health research studies with human beings, as well as that referring to the protection of personal data and clinical information derived from it. Under these premises, this protocol has been approved by the Regional Ethics Committee (committee code 4928, project code: AcuP, approval date 24 February 2021, record number 319).

Data collection notebooks will be handled in which only identification codes will appear that will correspond to the personal data in other guarded records. Similarly, electronic database-type records will be designed disaggregated to avoid identification of patients. An Informed Consent document has been prepared. The intervention does not require invasive tests or manipulation of biological samples beyond those implemented in routine clinical practice.

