## 2. Objectives and Hypothesis

The general objective is to assess the impact of the application of acupressure on obstetric and neonatal outcomes of labor. To achieve the general objective, four specific objectives have been established, each based on the verification or refutation of a specific hypothesis.

Objective 1: To analyze the possible statistical association between the use of acupressure and the times of cervical dilation and fetal delivery.

Null hypothesis: The dilation time and the expulsive time in the women who receive the intervention is the same as those of the women in the control group.Alternative hypothesis: The time of dilation and the time of expulsion in the women who receive the intervention is not the same as those in the women in the control group.

Objective 2: To compare the pain perceived by pregnant women in relation to the use of the acupressure technique.

Null hypothesis: The pain experienced by women receiving the intervention is the same as that experienced by women in the control group.Alternative hypothesis: The pain experienced by women receiving the intervention is not the same as that experienced by women in the control group.

Objective 3: To study the relationship between the use of acupressure and maternal satisfaction regarding the childbirth experience.

Null hypothesis: The satisfaction experienced about the birth process in women receiving the intervention is the same as that in women in the control group.Alternative hypothesis: The satisfaction experienced about the birth process in women who receive the intervention is not the same as that in women in the control group.

Objective 4: Assess the safety of the intervention through fetal and neonatal outcomes.

Null hypothesis: The fetal and neonatal results of the pregnant women belonging to the intervention group are the same as those in the pregnant women of the control group.Alternative hypothesis: The fetal and neonatal results of the pregnant women who belong to the intervention group are not the same as those in the pregnant women of the control group.

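### The 166 women randomised leave no margin for women without an expulsive time, so the stated 80% power holds only if almost none has a caesarean before full dilation

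*Protocol article*

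**What the plan says.** All the places below are in the protocol article, section 3.3 unless stated.

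- **Sample size.** Several calculations were run, and the largest, for expulsive-phase time, was adopted. The pilot values are "46 ± 39 min for the intervention group and 65 ± 47 min for the control group", with "alpha = 0.05 (type I error), power (1-beta) = 0.8, and allocation n1/n2 ratio = 1". The result is "obtaining a total of 166 women (83 in each group").
- **Outcome that sets the size.** The expulsive phase is the "second stage of parturition, which starts at full dilation and continues until birth".
- **Number randomised.** Recruitment ends when the calculated number is reached. Under Allocation, the R code draws 83 intervention positions from a list of exactly 166. No allowance for loss or for women without a value is stated.
- **Caesareans.** The recorded variables include "type of delivery termination (eutocic, instrumented, caesarean section"). Only earlier caesareans are an exclusion, so a caesarean in the current labour remains possible.
- **Purpose of the intervention.** Pressure on the first set of points is meant to make contractions regular and effective and to help the fetal head descend.
- **Analysis.** Under Data analysis: "For the comparison of means between dichotomous variables, the Student t-test and ANOVA test will be performed", with non-parametric tests if the parametric criteria fail.
- **Hypothesis.** Section 2, Objective 1, is two-sided: "the time of expulsion in the women who receive the intervention is not the same as" in the control group. It covers dilation time as well as expulsive time.

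**The concern.** A time that starts at full dilation does not exist for a woman who never reaches full dilation. If she is delivered by caesarean first, her dilation time is not completed either, so both Objective 1 outcomes are undefined for her. The sample size treats every randomised woman as supplying a value.

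Two things are at stake. The first is power, because each such woman reduces the number behind the calculation, and the recruitment target and the allocation list hold no reserve. The second is what is compared. The named tests need one completed time per woman. If they are run on the women who have one, the groups are those who reached full dilation, not those randomised. Reaching full dilation happens after randomisation, and the intervention is intended to affect progress towards it. If it does, the two subsets can differ in composition and the difference in minutes is biased. Recruiting more women would not remove that bias.

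**Working it through.** **Inputs.** From section 3.3: means 46 and 65 min, SDs 39 and 47 min, alpha 0.05, power 0.80, ratio 1:1. The test is taken as two-sided, from Objective 1 in section 2. The sample-size text does not state sidedness, but a one-sided test gives 65 per arm and does not reproduce the plan.

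**Step 1: reproduce the 166.**

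- Difference: 65 − 46 = 19 min.
- Common SD: √((39² + 47²)/2) = √((1521 + 2209)/2) = √1865 = 43.19 min.
- Standardised difference: d = 19/43.19 = 0.440.
- Two-sided two-sample t-test (noncentral t), 80% power: 82.07 per arm, rounded up to 83, so 2 × 83 = 166. This matches the plan exactly.

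**Step 2: look for slack.** Power by number per arm with a measured time, at d = 0.440:

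| Measured per arm | Power |
|---|---|
| 83 | 80.4% |
| 82 | 79.97% |
| 78 | 77.95% |

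One woman per arm without a value uses up the rounding margin.

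**Step 3: power if a share c of each arm has no expulsive time.** The number measured per arm is 83 × (1 − c). The documents give no value for c, so the shares below are assumptions. The last column is the total to randomise to keep 83 measured per arm, 2 × 83/(1 − c) with each arm rounded up.

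| c (assumed) | Measured per arm | Power with 166 randomised | Total to keep 83 measured per arm |
|---|---|---|---|
| 5% | 78.9 | 78.4% | 176 |
| 10% | 74.7 | 76.2% | 186 |
| 15% | 70.6 | 73.7% | 196 |
| 20% | 66.4 | 71.1% | 208 |

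Power drops below 78% once about 6% of each arm has no value (5 of 83, leaving 78).

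**Step 4: selection.** No arithmetic is possible here, because the documents give neither a caesarean rate nor an effect on it. The reasoning uses three statements: the outcome begins at full dilation, the intervention is meant to promote progress in labour, and the tests need a completed time. Together they mean that a comparison limited to women with a time conditions on a post-randomisation event. The direction of the bias cannot be derived.

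**The case against.** The strongest reply is that the shortfall may be small. The documents give no caesarean rate and no stage at which caesareans occur. A caesarean after full dilation still has an expulsive time under the protocol's definition. The entry criteria remove several groups of women, among them those with previous caesareans or non-cephalic presentation. At 5% without a value the loss is under two points, and the upper shares in the table have no support in the documents. By the protocol's account, the other sized outcomes (active phase, passive phase, VAS) needed fewer women. The Discussion already concedes that the sample size rests on a small pilot. All of this stands, and it limits the size of the point. It does not create a margin that the 166 lacks, and an analysis plan not shown here cannot supply women who were never recruited.

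A second reply is that no text drops women with caesareans, and that handling undefined times may be left to an analysis plan. That is fair. A reader might infer that the protocol limits the comparison to vaginal births, but it does not say so. The selection point is therefore conditional: it applies if the named tests are run on the women who have a time, and those tests offer no other route.

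Two further inferences are not supported:

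- **Instrumental births.** One might say these give falsely short times. The outcome runs to birth whatever the mode, so they have complete durations. Ending observation at an instrumental birth would probably be informative censoring and would still condition on full dilation.
- **Delivery mode among the independent variables.** One might read this as planned adjustment for a post-treatment event. The list is a general one that also holds birth weight and newborn arterial pH, and no stated analysis conditions on delivery mode.

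**Conclusion.** The point holds in a limited form. The 166 is arithmetically right for 166 women with an expulsive time, but it is applied as the number randomised. The 80% is met only if almost no woman lacks a value. Under assumed shares of 5 to 20%, power is about 78 to 71%. These figures rest on the pilot difference and SDs being correct, the t-test being used, and equal loss in both arms. The article does not say whether the pilot means cover all 17 and 23 women or only those who reached the second stage.

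A reader might conclude that 80% power is certainly missed by a wide margin. The documents do not show that, because the share is unknown and the loss could be about two points.

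The selection problem does not depend on the size of the power loss. A comparison restricted to women with a time is not a comparison of the randomised groups, and its bias has no known direction.

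**What to change.** 1. Restate the power for the number of women expected to have an expulsive time, over a range of shares. The 40 women included to date can inform the range. They cannot fix it, since each of them moves the share by 1/40 = 2.5 percentage points.
2. Add an analysis of all randomised women: time from first application to vaginal birth, with caesarean as a competing event. The start time of the technique is already recorded. The time of birth, by either route, is also needed and should be confirmed as captured.
3. Report delivery mode by arm as an outcome beside the expulsive-time comparison, so that readers can judge how far the women with a time differ in make-up between arms.

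The cost is a slightly lower stated power, some analysis wording and one more model. That model addresses a different outcome from the one that sized the trial, and the pilot figures given do not establish its power. The protocol should say so and not carry the 80% over to it.

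### The 80% power for expulsive time needs 83 measured times per group, but 83 is also the number of women to be included, with no allowance for women who never reach full dilation

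*Protocol article*

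**What the plan says.** All of this is in section 3.3 of the protocol article, apart from the hypothesis in section 2.

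- **Basis of the calculation.** Several calculations were made, and the one demanding the most women, for the expulsive phase, was adopted. Its inputs are "46 ± 39 min for the intervention group and 65 ± 47 min for the control group" and "alpha = 0.05 (type I error), power (1-beta) = 0.8, and allocation n1/n2 ratio = 1".
- **Result.** "obtaining a total of 166 women (83 in each group").
- **Outcome.** The expulsive phase is the "second stage of parturition, which starts at full dilation and continues until birth".
- **Hypothesis (section 2, Objective 1).** "The time of dilation and the time of expulsion in the women who receive the intervention is not the same" as in the control group, so the test is two-sided.
- **When inclusion ends.** Eligible women under the principal investigator's care "will be included until the predetermined sample size is reached".
- **Allocation list.** The random sequence is drawn with "sample (1:166, 83, replace = FALSE"), and women are matched to it in order of arrival. The list has 166 positions, 83 of them for intervention.
- **How labour may end.** Among the clinical variables is "type of delivery termination (eutocic, instrumented, caesarean section"). No caesarean rate is given.

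The article states no allowance for women without an expulsive time, and no rule for replacing them.

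**The concern.** A sample size formula for two means returns the number of observed values needed in each group. Here that number is carried over, without change, as the number of women who enter the trial. The two agree only if every woman entered supplies a value.

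The definition of the outcome means that this is not assured. A woman delivered by caesarean before full dilation never enters the second stage, so she has no expulsive time. The recorded variables provide for caesarean delivery, and although previous caesarean is an exclusion, nothing excludes one in the current labour. Induced labours and first births are eligible.

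What is at stake is whether 80% describes the trial as it will be run. Expulsive time was chosen as the most demanding outcome so that the other analyses would be covered too, so it is the outcome with the least room for loss.

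**Working it through.** **Inputs.** Means 46 and 65 min, standard deviations 39 and 47 min, alpha 0.05, power 0.80 and ratio 1 (section 3.3); two-sided test (section 2).

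**Step 1: reproduce the plan's figure.**

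- Difference = 65 − 46 = 19 min.
- Pooled SD = √((39² + 47²)/2) = √((1521 + 2209)/2) = √1865 = 43.19 min.
- Standardised difference d = 19/43.19 = 0.440.
- The two-sided, two-sample t-test (noncentral t) needs n = 82.07 per group, rounded up to **83**, or 166 in total. This is the stated figure.
- The normal approximation gives 82. A one-sided test gives 64 by the same approximation and does not reproduce the figure.

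**Step 2: is there slack in 83?** Power is 0.8045 with 83 values per group and 0.7997 with 82. Rounding up from 82.07 leaves less than one woman per group, so no allowance is hidden in the figure.

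**Step 3: power when a share r of the 166 women has no value.** The article gives no r, so the shares below are assumptions. Evaluable number per group = 83 × (1 − r), with the same share lost in each group and the same d.

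| Assumed share without an expulsive time | Evaluable per group | Power |
|---|---|---|
| 0% | 83 | 0.804 |
| 5% | 78.85 | 0.784 |
| 10% | 74.70 | 0.762 |
| 15% | 70.55 | 0.737 |
| 20% | 66.40 | 0.711 |

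**Step 4: where the loss becomes noticeable.** At r = 6%, 83 × 0.94 = 78.02 per group. Power at 78 is 0.7795, which is just over 2 points below 80%.

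**Step 5: what holding 80% would take, for reference.** Dividing 83 by (1 − r) and rounding up gives 88 per group at 5%, 93 at 10%, 98 at 15% and 104 at 20%.

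**The case against.** The case on the other side is substantial.

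- **The calculation is correct.** This stands in full. A reader might infer that 166 is a miscalculation. It is not: the stated inputs reproduce it exactly.
- **The source is a condensed article.** A rule for non-evaluable women may sit in a full protocol or analysis plan that is not shown. This has some weight. An analysis plan could say how such women enter the comparison, but it could not supply measured times beyond a list that the article itself fixes at 166 positions. Nor would another way of counting those women be the comparison for which the 80% was calculated.
- **Caesarean is listed, not predicted.** Also true. It is one category of a recorded variable. The eligibility criteria require no associated pathology and exclude previous caesarean, breech or transverse presentation, placenta previa, impaired fetal growth and abnormal fluid volume. A caesarean after full dilation still has an interval to birth, as does an instrumental birth. Only caesareans before full dilation certainly lose the value.
- **Withdrawals add little.** The outcome is observed within a single labour under the principal investigator's own care and needs no follow-up visit.
- **Other uncertainty is larger.** The planning difference comes from 17 and 23 women. Weighting the SD by those numbers gives √((16 × 39² + 22 × 47²)/38) = 43.81 and power of 0.793 at 83 per group, about the same effect as losing two women per group (0.795 at 81). The Discussion already acknowledges the small pilot as a limitation, but it does not mention women without a second stage.

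These points limit the size of the shortfall. They do not change the fact that the number of values needed and the number of women included have been set equal.

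**Conclusion.** The point holds as a qualification of the stated power, not as an error in the sample size. The figure of 83 per group is the bare number of measured expulsive times for 80% power. The protocol uses it as the number of women included, although its own outcome definition and delivery categories allow for women with no value. The power of 166 included women is therefore below the stated 80% to the extent that such women occur.

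The size is unknown, because the documents give no rate. Under the assumed shares it runs from less than 2 points below 80% at 5% missing to about 9 points at 20% (80 − 71). These figures assume equal loss in both groups, the pilot difference and standard deviations as stated, and a two-sided t-test on observed times.

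A reader might infer that the trial is seriously underpowered, or that the abstract's power claim is wrong. The documents support neither. Nothing in them establishes a share as high as 15% or 20%, and the abstract speaks only of adequate power, without a figure. The point is also confined to expulsive time: the calculations for the other outcomes gave smaller numbers, which the article does not print.

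**What to change.** In section 3.3, after the sample size result:

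1. State that 83 women per group with an observed expulsive time give 80% power.
2. Report the share without an expulsive time among the women already recruited, pooled over both groups so that nothing is disclosed by group. Section 4 reports 40 such women, so the count should be available. Each woman is 2.5% of 40, so give the numerator and denominator.
3. Restate the power of 166 included women at that share, by the calculation in step 3 above.

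No assumed rate, such as 10 to 20%, should be written in as though it were known. The abstract needs no change.

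The cost is two or three sentences and a stated power that may be slightly less favourable. No extra women are required. If the sponsor prefers to keep 80%, the alternative is to divide 83 by one minus the reported share and lengthen the allocation list to match, at the cost of more recruitment.
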